### Interventions

#### Yoga program (active intervention)

Participants randomized to the yoga group will complete a gentle *Iyengar* yoga program based on that developed and successfully implemented in our pilot studies [15, 66]. The yoga program was finalized following detailed review and input from an *Iyengar* Master Trainer.

Program logistics: yoga group participants will attend two 75-min classes per week for the first 4 weeks, then one 75-min class for the remaining 8 weeks, and will be asked to complete a 30-min homework routine 5 days/week on non-class days. Yoga classes will be held at two yoga studios in close proximity to the WVU Health Sciences Center campus (WVU site) and OSU Center for Integrative Health and Wellness (OSU site), respectively. As in our previous trials [15, 66], each yoga class will begin with simple yogic centering and breathing exercises, followed by a sequence of active and restorative poses, and ending with a 10-min guided supine relaxation practice. The yoga routines, including a collective total of 25 common *asanas*, have been tailored for sedentary adults naïve to yoga, gradually increasing in difficulty as students progress. Pose modifications and props (e.g., chairs, blankets, and straps) will be used as needed to enable participants to perform the poses safely and easily, regardless of their level of physical ability or fitness. In addition, each class will be restricted to no more than 12 participants to allow for personalized attention. The home practice (see Table 1) will be performed with the aid of a yoga DVD and a comprehensive, indexed training manual illustrating the homework routines; These guides are based on materials developed for our preliminary trials and modified to reflect the extension to a 12-week intervention period for the proposed study. Participants will also be provided yoga mats and straps to facilitate home practice.

**Table 1 Tab1:** Yoga home practice routines

Home Practice 1: Weeks 1–3 (*use wall for side-angle standing poses*)	
1. Upward extended-leg pose	*Urdhva Prasarita Padasana*
2. Straight-leg pose: (a) bent knee 3x, (b) straight leg 2x	*Supta Padangusthasana*
3. Upward extended arms in mountain pose: (a) palms forward, (b) palms facing	*Urdhva Hastasana in Tadasana*
4. Extended side-angle pose	*Utthita Parsvakonasana*
5. Half-intense pose: (a) hands to wall, (b) hands on chair	*Ardha Uttanasana*
6. Extended triangle pose	*Utthita Trikonasana*

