5. Intense pose: holding elbows	*Uttanasana*
6. Downward-facing dog pose	*Adho Mukha Svanasana*
7. Warrior I pose: back heel at wall	*Virabhadrasana I*
8. Hero’s pose	*Virasana*
9. Garland pose: (a) hold elbows, (b) extend arms	*Malasana*
10. Bound angle pose	*Baddha Konasana*
11. Head-to-knee pose	*Janu Sirsasana*
12. Western intense pose	*Paschimottanasana*
13. Active bridge pose	*Chatush padasana*
14. Corpse pose	*Savasana*
15. Corpse pose with breathing	*Savasana Pranayama*

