#### Criteria for discontinuing or modifying allocated interventions for a given trial participant

Each class will be restricted to no more than 12 participants to allow for personalized attention. In the event that a participant experiences an adverse event (AE) which makes continuation of the intervention unsafe for that individual, the study coordinator will inform the principal investigator (PI) and the study physician, referencing just the participant’s study ID number, and the intervention will be discontinued for that participant. With their permission, participants will continue to be followed if the study intervention is discontinued. Any AE requiring discontinuation that is judged to be due to the intervention will prompt re-evaluation and possible modification of the intervention.

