#### Blinding

The majority of study personnel will be blinded to treatment assignment until the database is deidentified and locked. The randomization scheme will be devised and provided by an individual with statistical expertise who has no access to the data or influence on study outcomes; this individual will maintain the master coding sheet indicating the treatment assignment corresponding to each participant number. Following confirmation of eligibility and baseline assessment, randomization will be performed by the consenting team member, who will have no advance knowledge of treatment allocation; sealed, opaque envelopes containing information regarding the participant’s assigned intervention will simply be uniquely numbered, with no external indication of treatment assignment; as in previous studies, participants will be instructed to open their envelopes upon exiting the building. The study coordinator will maintain the list linking participant numbers with personally identifiable information. Assessments will likewise be conducted by trained study personnel blinded to treatment allocation and specifically hired for this purpose. The yoga and educational film group instructors will be responsible for documenting attendance and collecting homework logs, as well as for contacting participants. Instructors will not have access to the data or be involved in data monitoring or analysis. Data will be entered (double-keyed) into an existing data template by two students trained in data management; participants will be identified only using a unique number.

In the unlikely event that there are three serious adverse events (SAEs) in either group that are judged to be related to the intervention, the study coordinator will inform the PI of this fact. Up to this point, the PI will be aware of all SAEs but will be unaware of the affected participant’s group assignment. If the PI agrees that the SAEs are related to the intervention, she will determine that the blind will be broken. In that event, the study coordinator will give the list linking participant numbers with personally identifiable information to the PI.

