### Data management

Completed data forms or other hard-copy documents containing protected health information will be kept in a locked file in an investigator’s office. Data will be entered into an electronic deidentified database by authorized study team members, checked for completeness and accuracy. The PI or study staff will review all data collection forms on an ongoing basis for data completeness and accuracy as well as protocol compliance. Access to data with identifiers will be restricted to authorized study team members and regulatory authorities. Data verification will be performed by someone other than the individual originally collecting the data, or by double-data entry.

Electronic data will be stored on a secure server which is maintained, with regular back-ups, by WVU Health Sciences Center system administrators and accessible from password-protected computers in the WVU Department of Epidemiology. Any data, forms, and other records with identifiers that leave the site will be transported in a locked file box to maintain confidentiality. Identifiable data will be destroyed 5 years after study completion or 3 years after the last publication based on when the data is published, whichever comes last (unless future regulations dictate that the data be kept for longer).

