### Data monitoring, harms, and auditing

The frequency of data review for this study differs according to the type of data and can be summarized as follows: data on accrual, status of all enrolled subjects, adherence, and AEs will be reviewed by the PI and study coordinator every 4 months; accrual and AEs will also be reviewed yearly by the PI, IRB, Independent Monitoring Committee (IMC) (comprising three experts with appropriate expertise and experience in clinical trials, biostatistics, and clinical medicine), and NCCIH; SAEs will be reviewed per occurrence by all.

While both programs are minimal risk interventions, we are further ensuring participant safety by: using highly trained *Iyengar* instructors experienced in teaching adults with chronic health conditions and in adapting poses to minimize discomfort and risk of injury; including only gentle postures in the program; and maintaining small class sizes to ensure adequate personalized attention. In addition, all participants will be encouraged to report any AEs to study staff and on their yoga and co-intervention logs. Yoga group participants will also be queried about AEs by the yoga instructors during class. Yoga instructors will notify the study coordinator regarding any AE.

The study coordinator will promptly report AEs to the IRB according to protocol and IRB policies; complete an adverse events form and grade the AE; and contact the participant by telephone on a weekly basis to monitor the event until the event resolves, the study is completed, or the participant is removed from the study. In addition, subjects can choose to stop the study at any time. Any serious and unexpected AEs will require re-evaluation of the risk of the study. Monitoring and aggregate review will be performed by the PI, IRB, and IMC through annual review.

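### Weekly adverse-event calls stop at study completion or removal even if the event is open, with no later contact provided for serious or intervention-caused events

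*Protocol article*

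**What the plan says.** Under Data monitoring, harms, and auditing, the study coordinator reports each adverse event to the IRB, completes and grades a form, and telephones the participant weekly "until the event resolves, the study is completed, or the participant is removed from the study". The rule covers adverse events of every kind.

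The other safety provisions are these:
- Same section: "SAEs will be reviewed per occurrence by all", and serious unexpected events lead to a fresh look at the study's risk.
- Criteria for discontinuing or modifying allocated interventions: "With their permission, participants will continue to be followed if the study intervention is discontinued". An event that requires discontinuation and is judged due to the intervention leads to re-evaluation of the intervention.
- Blinding: the coordinator alerts the principal investigator if there are "three serious adverse events (SAEs) in either group that are judged to be related to the intervention".
- Stopping rules: safety grounds on which the whole trial may be halted.

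**The concern.** The three end points are alternatives, so the first one reached ends the calls. Resolution is a natural end. Completion and removal are administrative: they say nothing about the state of the event, and the rule makes no exception for a serious event or one the yoga or film program caused.

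At stake are the safety of a participant whose serious event is still open, and knowledge of how such events end. The trial is meant to prepare a larger one, and the article presents yoga as a safer option than drug treatment. In a trial of 44 people there will be few serious or related events, so each unknown outcome counts. No statistical result is at stake.

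**Working it through.** There is no figure to reproduce. The check has three parts: whether any other section extends contact, how far each administrative end point reaches, and whether late events are possible.

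**1. Does another section extend contact?**

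| Provision | What it does | Contact after completion or removal? |
|---|---|---|
| Continued follow-up with permission (discontinuation criteria) | Applies when the intervention is stopped | No; it does not mention removal from the study or the time after completion |
| Per-occurrence review of serious events (data monitoring) | Informs the oversight bodies | No; a review is not contact with the participant |
| Re-evaluation of risk or of the intervention | Acts on the study or program | No |
| Three related serious events (Blinding) | Leads to possible unblinding | No |
| Stopping rules | Act on the trial | No |

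None does.

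**2. Reach of each end point.**

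*Removal.* An event that makes the intervention unsafe leads to stopping the intervention, and follow-up then continues with permission. The main event-driven route is therefore covered. What remains is removal from the study by some other route, which the article does not describe.

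*Completion.* Data management and Stopping rules use completion in the sense of the whole trial. On that reading, earlier cohorts can still be called while later ones run, and the limit falls mainly on the last cohort. Consent and screening plans at least 15 participants per cohort, and 44 are to be randomised. If the minimum holds, the last cohort is at least 15 / 44 = 34% of participants. That is a share of participants, not of events: only those with a qualifying event still open at that time are affected. If completion instead meant each participant's own week-12 visit, the limit would apply in every cohort.

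**3. Are late events possible?** The yoga program section describes routines "gradually increasing in difficulty as students progress". Counting distinct asanas in Table 1 by first appearance in home practice:

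| Weeks | New asanas |
|---|---|
| 1–3 | 12 |
| 4–6 | 4 |
| 7–9 | 3 |
| 10–12 | 6 |

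12 + 4 + 3 + 6 = 25, which matches the total of 25 given in the text. The six that are new in weeks 10–12 include "Warrior I pose: back heel at wall"; the others are Virasana, Malasana, Janu Sirsasana, Paschimottanasana and Chatush padasana. Home Practice 4 has 15 items, so 6 of 15 are new. Classes may introduce a pose earlier, and no risk is attached to any pose. The count shows that late events are possible, not how often they occur.

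**The case against.** The strongest objection is that this is a condensed article. Follow-up of serious events is often set out in a full protocol or safety monitoring plan, and the article says that events are reported according to protocol and IRB policies. A fuller document could well contain the missing exception. That lowers confidence, but the article is not silent here: it prints the end points, and two of them override the state of the event. The point is about a stated rule.

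The second objection is about reach. The discontinuation section covers most event-driven stopping, the completion limit falls mainly on the last cohort, and the article calls both programs minimal risk. If removal mostly means that the participant withdrew, further calls would need a permission that may have been refused. All of this stands and is why the point is minor.

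Three stronger readings are tempting and should not be drawn.
- A reader might infer that the outcomes of open serious events go unrecorded. The text limits the weekly calls; it does not say that. The oversight bodies know of each serious event, and an outcome could reach them by a route not shown.
- A reader might take the late poses as evidence of many late injuries. The article gives no event rate to support this.
- A reader might suppose that every adverse event is already classified as related or not, so that all related events could be followed longer at no extra effort. A relatedness judgement is described only for serious events and for events requiring discontinuation. For events in general the article mentions a form and a grade.

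**Conclusion.** The point holds as a cheap improvement. As written, the only participant contact about an adverse event that the article describes ends at study completion or removal whatever the state of the event, with no exception for serious events or those judged due to the intervention.

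The number affected is probably very small and cannot be estimated. No feasibility benchmark, sample size or effect-size estimate depends on it. The benefit is participant safety and complete outcomes for the few events that matter most to the next trial.

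This rests on two assumptions: that study completion is meant at trial level (a participant-level meaning would widen the gap), and that no fuller document already provides longer follow-up (if one does, the article's sentence only needs aligning with it). Confidence is medium.

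**What to change.** Amend the sentence in Data monitoring, harms, and auditing along these lines: serious adverse events, and adverse events requiring discontinuation that are judged due to the intervention, if still open at study completion or at removal from the study, will be followed by the study coordinator in both arms until resolution or stabilisation, or until the participant withdraws permission; the outcome and its date will be recorded. Other adverse events keep the present end points.

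This scope stays within the categories for which the article already describes a relatedness judgement, so it adds no new classification. The means largely exist: the Blinding section says "The study coordinator will maintain the list linking participant numbers with personally identifiable information", and Data management says "Identifiable data will be destroyed 5 years after study completion or 3 years after the last publication", whichever is later, so contact details remain for at least 5 years after completion.

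The cost is a few extra calls, some coordinator time after completion, and possibly a later close of adverse-event data. Under Ethics and dissemination, significant changes need prior approval from the WVU IRB and NCCIH, so the amendment may need both. The consent wording, which is not shown, should be checked to confirm that it allows contact after removal. Enrolment was open when the article was published, so the change could still take effect.

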#### Stopping rules

This study will be stopped prior to its completion if: (1) the intervention is associated with adverse effects that call into question the safety of the intervention; (2) any new information becomes available during the trial that necessitates stopping the trial; or (3) other situations occur that might warrant stopping the trial. Because this RCT is specifically designed to be a feasibility study, and we will be investigating recruitment rates and optimal recruitment strategies as part of our primary aim, slow accrual would not comprise a justification for stopping the trial.

In addition, the study may be discontinued at any time by the IRB, NCCIH, the OHRP, or other government agencies as part of their duties to ensure that research participants are protected.

## Discussion

In summary, RLS is a common and burdensome sleep disorder associated with profound impairment of health, well-being, and quality of life, and with significant personal, societal, and economic burden [6, 7, 26]. There is no cure for RLS, and current front-line drug therapies can carry severe side effects. If, as our promising preliminary data suggests, yoga ultimately proves feasible and effective in reducing RLS symptoms and symptom burden, yoga will offer a novel, safe, and likely cost-effective approach to RLS prevention and management, targeting not only RLS symptoms, but also likely contributing factors and common comorbidities.

This study will lay the essential groundwork for a planned larger RCT to determine the efficacy of a yoga program for reducing symptoms and the associated burden of RLS, a common and potentially debilitating sleep disorder. Specifically, central goals of this trial include evaluating the feasibility and acceptability of a 12-week RCT of yoga vs. an attention control, and optimizing the yoga protocol for a planned larger trial of yoga for RLS management; we will also obtain effect size estimates for specific outcomes of relevance to RLS management, information critical to designing and powering our planned future study. Based on our strong pilot data, the study is consistent with the urgent national need to curtail spiraling health care costs and to identify sustainable, potentially cost-effective new approaches to chronic disease management. If the findings of the current trial and the subsequent larger RCT are positive, this study will also help support a new approach to clinical treatment of this challenging disorder, help foster improved understanding of RLS etiology, and ultimately contribute to reducing the individual, societal, and economic burden associated with this condition.

### Ethics and dissemination

This study has been approved by the West Virginia University Institutional Review Board (IRB#1505699758). No significant changes will be made to this protocol without the prior approval of the WVU IRB and the NCCIH. As described above, each participant will provide written informed consent prior to the initiation of baseline assessments or the intervention.

#### Confidentiality

During this study, medical history, vital signs, and assessment questionnaires will be completed at baseline and at regular intervals during the study. All of the material collected are for research purposes only, and data will be kept in strict confidence. Information will not be released without written permission of the participant, except as necessary for monitoring by the IRB, the NCCIH, the OHRP, and the IMC. Confidentiality will be ensured by use of identification codes. This data, collected at the assessment visits, will be identified with a study identification code unique to the subject.

#### Dissemination plans

Upon completion of the trial, the authors plan to present the study findings at conferences aimed at physicians typically treating patients with RLS, and at other integrative health care practitioners such as yoga therapists. In addition, the investigators plan to submit our findings for publication in relevant peer-reviewed journals; we do not intend to hire professional writers.

## Trial status

This trial is currently open for enrollment.

## Abbreviations

BMI: Body Mass Index (weight(kg)/height(m)^2^)
BP: Blood pressure
CEQ: Credibility/Expectancy Questionnaire
DSSI: Duke Social Support Index
HR: Heart rate
IRLS: International Restless Legs Scale
PASE: Physical Activity Scale for the Elderly
POMS: Profile of Mood States
PSQI: Pittsburgh Sleep Quality Index
PSS: Perceived Stress Scale
SF-36: 36-item MOS Short Form-36
Tx: Treatment
